#### Descriptive analysis

Continuous variables will be reported as mean±SD and categorical variables as frequencies with corresponding percentages.

#### Prediction model development

We will compare a machine learning and logistic regression approach to prediction model development for incident AF in CPRD-GOLD. Logistic regression model offers a more manageable approach for implementation, interpretation and training compared with machine learning algorithms, but machine learning methods can better handle non-linearities and interactions among variables and may lead to better discriminative performance.^19^

We will investigate the use of a random forest (RF) classifier for AF prediction in the CPRD-GOLD dataset. In our systematic review of AF prediction in EHRs, it had the most evidence for use and showed robust performance in different datasets and geographies.^19^ RF is an ensemble technique that combines a large number of decision trees using a bagging approach to improve the overall performance (figure 2).^35^ In brief, the bagging approach grows multiple classification trees in parallel where each tree gives a classification which is called votes. These votes are then aggregated to provide a more accurate and stable prediction. Furthermore, the degree of variation of each feature in an RF classifier for the prediction task can be calculated using the mean decrease in the Gini coefficient, a measure of how each variable contributes to the homogeneity of nodes and leaves in the resulting RF. Showing the importance of variables used in prediction (explainability) is considered important for clinical uptake of prediction models,^36^ and a limitation of using deep learning techniques. The RF model will be trained in the training dataset to predict a binary classification of developing AF or not. The model will return the probability between 0 and 1 for developing AF in the training set, corresponding to the predicted probabilities of developing AF.

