### Data analysis plan

#### Data preprocessing

The CPRD-GOLD and CHS data will be cleaned and preprocessed for model development, internal validation and external validation. Specifically, for patient features with binary values, 0 and 1 will be mapped to the binary values. Variables with multiple categories (ethnicity) will be split into their component categories, and each given a binary value to indicate the presence or not of the variable for each patient. Continuous variables (age) will be kept as continuous.

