**Figure 2 F2:**
[figure not shown]
A schematic representation of a multivariable logistic regression model or random forest model using data from electronic health records to provide risk prediction for incident AF. AF, atrial fibrillation.

Preprocessed patient-level data in CPRD-GOLD will be randomly split into an 80:20 ratio to create derivation and internal validation (or training and testing) samples. The split ratio is not a significant factor, given the volume of the sample size. The model parameters and drop-out rate will be chosen through a grid search and 10-fold cross-validation will be used (ie, 10% of the training data will be randomly selected as the cross-validation set). The multivariable logistic regression model will be developed with backward model selection with Akaike information criterion.^37^ The prediction window will be set at 6 months, as this is considered in keeping with the logistical time frames for organising AF investigation at scale.

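### The random forest is described by class votes but used as a 6-month risk; for so rare an outcome the plan should specify averaged leaf proportions and a flexible age term in the logistic comparator

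*Protocol article*

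**What the plan says.** All statements are in the Data analysis plan of the protocol article.

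**Forest (Prediction model development).** The method is introduced as a classifier in which "the bagging approach grows multiple classification trees in parallel where each tree gives a classification which is called votes". The next step is "These votes are then aggregated to provide a more accurate and stable prediction". The training target is "The RF model will be trained in the training dataset to predict a binary classification of developing AF or not". The section then states that "The model will return the probability between 0 and 1 for developing AF in the training set" and treats these values as predicted probabilities. Voting is the only aggregation described. On tuning, "The model parameters and drop-out rate will be chosen through a grid search and 10-fold cross-validation will be used"; the loss, leaf size, number of trees and any class weighting are not given. On the horizon, "The prediction window will be set at 6 months".

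**Logistic model.** Under Data preprocessing, "Continuous variables (age) will be kept as continuous". Under Prediction model development, "The multivariable logistic regression model will be developed with backward model selection with Akaike information criterion". No spline or interaction term is mentioned. The same section gives the handling of non-linearities and interactions as a reason for using machine learning.

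**Use of the output.** Internal validation plans AUROC, Brier score, calibration plot and slope, decision curves, and net reclassification at a threshold equal to the cohort's average 6-month incidence. External validation sends the saved model to CHS to generate a 6-month probability for each patient.

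**The concern.** A tree that votes returns AF only when AF is the majority class in the leaf the patient reaches. When about 1 person in 500 has the event, an AF majority is very unlikely in a leaf of more than a few people, even in a high-risk group. The share of trees voting AF is then not an estimate of risk: it is close to zero for almost everyone. Re-weighting the classes removes the zeros but moves the vote share far above the true risk.

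Most of the planned measures need a number on the risk scale. If the vote share collapses, the reclassification index, decision curves, calibration slope and AUROC all suffer. If votes come from balanced classes, ranking may survive but everything tied to a risk threshold does not. The same values would be carried into CHS.

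A separate matter concerns the comparator. If age enters the logistic model as a single straight line while the forest is free to bend, a forest advantage could reflect one missing spline rather than a better method.

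**Working it through.** The article states no figure for the forest's output, so there is none to reproduce. The nearest stated inputs are the CHS counts.

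**1. Incidence.** From Data sources and permissions: 4330 / 2,159,663 = 0.2005% over 6 months in CHS. For CPRD-GOLD the article gives only AF at any time in follow-up, so 0.2% there is an assumption.

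**2. Chance that a leaf votes AF.** For a leaf of n people who share risk q, treated as a random draw, this is P(Binomial(n, q) > n/2).

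| True risk q | n = 1 | n = 3 | n = 5 | n = 11 |
|---|---|---|---|---|
| 0.2% | 0.002 | 1.2e-5 | 8.0e-8 | 2.9e-14 |
| 1% | 0.010 | 3.0e-4 | 9.9e-6 | 4.4e-10 |
| 5% | 0.050 | 7.3e-3 | 1.16e-3 | 5.8e-6 |

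The expected leaf proportion is q in every cell. At n = 5 a true 5% risk would appear as 0.116%, which is 0.05 / 0.00116, or about 43 times too low.

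**3. Granularity.** With 500 independent trees (assumed), one vote is 1/500 = 0.2%, about the whole reclassification threshold if CPRD-GOLD resembles CHS. A person at 0.2% risk receives no AF vote with probability (1 − 0.002005)^500 = 0.37 for single-person leaves, and 0.99996 for leaves of five.

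**4. Fitted trees.** Step 2 ignores that splits seek purity, so forests were fitted to simulated data: age plus 30 binary codes (assumed), mean true risk 0.17%, 150,000 training records (268 events) and 100,000 test records (161 events), with 150 trees at leaf size 1 and 200 otherwise. The AUROC of the true risk was 0.81.

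| Minimum leaf | Output | Mean | Exactly zero | AUROC |
|---|---|---|---|---|
| 1 | votes | 0.0020 | 91% | 0.58 |
| 1 | leaf mean | 0.0021 | 91% | 0.59 |
| 10 | votes | 0 | 100% | 0.50 |
| 10 | leaf mean | 0.0018 | 12.5% | 0.75 |
| 200 | votes | 0 | 100% | 0.50 |
| 200 | leaf mean | 0.0018 | 0% | 0.80 |
| 200, balanced | votes | 0.345 | 1.2% | 0.79 |
| 200, balanced | leaf mean | 0.319 | 0% | 0.80 |

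A logistic model on the same data had mean 0.0018 and AUROC 0.80. The data were generated from a logistic model with linear age, so that figure says nothing about forest against logistic. With 161 test events, differences of a few hundredths are noise.

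**5. Effect at a 0.2% threshold.** With 200 trees the smallest non-zero vote share is 1/200 = 0.5%, so under balanced votes 1 − 0.0115 = 98.9% of people lie above the threshold. With unweighted votes at leaf size 10 or 200, nobody does. At leaf size 1, 74.5% of true cases have no vote, so sensitivity is 1 − 0.745 = 25.5%.

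**6. Brier score.** At incidence p = 0.002005, predicting zero for everyone scores p = 0.002005; predicting the mean for everyone scores p(1 − p) = 0.002001. The Brier score would hardly register a collapse.

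**7. Age.** Assume log-odds concave in age (quadratic term −0.08 to −0.15 per decade squared, ages 31 to 95, mean risk 0.2%). Across 18 assumed combinations of age distribution and slope, a straight line over-predicts at 31 to 45 years by 1.5 to 5.1 times and under-predicts at 60 to 75 years by 6% to 27%. The curvature has no source in the article; only the direction was the same throughout.

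**The case against.** The voting sentences are a brief general account of bagging. The statement about this model is that it returns a probability, and nothing says that this is the raw share of majority votes. Leaf size, number of trees and class weights are settings an article commonly leaves to a fuller plan. **This stands**, and it means that collapse is conditional on implementation, not planned.

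The binomial figures treat a leaf as a random draw with a common risk, which fitted trees are not. **This stands** for the 43-fold figure; the simulation drops that assumption but rests on invented covariates.

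Tuning would reject a useless setting, and the planned validation would expose one. **This stands only in part.** An AUROC of 0.50 would be noticed, and so would a poor calibration plot. But no unweighted vote setting tried did better than 0.58, so tuning leaf size within a vote forest offers no good choice. Balanced votes pass on AUROC while being far off on the risk scale. Validation detects the fault after development, and no recalibration step is stated.

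Averaging leaf proportions is not enough alone: with single-person leaves it does no better than votes. **This stands**, and is why node size belongs in the fix.

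Keeping age continuous rules out neither splines nor interactions, and setting a simple model against a flexible one is a declared purpose. **This stands** against any claim that a linear age term is fixed. It does not remove the difficulty of interpreting a forest advantage if the age term does turn out linear.

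**Conclusion.** The point holds as a low-cost improvement to an estimator that is loosely fixed, not as a demonstrated error. The only aggregation described is class voting, and the result is used as a 6-month probability. For an outcome near 0.2%, unweighted votes from leaves of more than a few people go towards zero, and balanced votes overshoot (a mean of 0.35 against a true mean of 0.0017 in the simulation). Either would damage the risk-scale measures under Internal validation and the probabilities generated in CHS.

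The conclusion assumes that CPRD-GOLD's 6-month incidence resembles that of CHS and that the vote description is implemented literally. The leaf-majority, simulation and age-curvature figures show mechanism and direction only.

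Two stronger readings are not supported. A reader might infer that the planned forest will collapse; the article does not state the settings that decide this. A reader might also infer that vote pooling against backward AIC selection by itself makes the comparison unequal. It does not: both models are built in the same data under one 80:20 split and judged by common measures. The fairness question rests only on the form of the age term, which the article leaves open.

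**What to change.** 1. State that the forest is a probability forest: its prediction is the average across trees of the AF proportion in the terminal node.
2. Tune node size by cross-validated log-loss or Brier score. Log-loss is preferable here, because the Brier score barely separates all-zero predictions from the mean.
3. If classes are weighted or re-sampled, recalibrate within the training data before any measure on the risk scale is computed and before the model file goes to CHS.
4. In the full logistic model, enter age as a restricted cubic spline, and compare the two methods on the same folds and test set.

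The cost is a few sentences, a software setting in R and a few extra model terms, provided it is done before models are fitted. The downside is a slightly less simple age effect. The calculator may keep a simpler age term if its calibration by age is adequate.

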Candidate variable data types are deliberately limited to ensure widespread applicability of the model given the reality of ‘missing’ data in routinely collected EHRs.^17^ Observations and laboratory results are not included. Ethnicity information is routinely collected in the UK NHS and so has increasingly high completeness,^32^ and we will include an ‘ethnicity unrecorded’ category where it is unavailable because missingness is considered informative.^33^ Ethnicity in a UK context does not directly translate to an Israeli context so sociodemographic surrogates will be used: (1) population sectors—General Jewish, ultra-orthodox Jewish and Arab and (2) Socioeconomic score on a scale of 1–10. For diagnoses, if a medical code is present in the patient record (without a preceding time window limitation) then the variable is classified as being present for the patient. If medical codes are absent in a patient record we will assume that the patient does not have that diagnosis, or that the diagnosis was not considered sufficiently important to have been recorded by the GP in case of symptoms.^34^ Concordantly, the analytical cohorts are not expected to have missing data for any of the predictor variables. It is possible that diagnoses may be recorded as free text, data to which we do not have access, rather than as diagnostic codes and this may lead to misclassification of some patients.

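### Mean decrease in Gini is the only importance measure named; with continuous age beside 0/1 codes and a rare outcome, a ranking reported this way could mislead on which conditions matter

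*Protocol article*

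**What the plan says.** The protocol article, Prediction model development, describes the random forest and says that the contribution of each feature "can be calculated using the mean decrease in the Gini coefficient". The next sentence gives the purpose: "Showing the importance of variables used in prediction (explainability) is considered important for clinical uptake of prediction models". The same sentence calls the lack of this a limitation of deep learning. No other importance measure is named.

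The scale of the predictors is set under Data preprocessing:
- age: "Continuous variables (age) will be kept as continuous";
- binary features: "for patient features with binary values, 0 and 1 will be mapped to the binary values";
- ethnicity: "Variables with multiple categories (ethnicity) will be split into their component categories", each with its own binary indicator.

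Under Predictor variables, "Observations and laboratory results are not included". Age is therefore the only many-valued predictor named for the CPRD-GOLD model.

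Tuning is described after Figure 2: "The model parameters and drop-out rate will be chosen through a grid search". Leaf size and tree depth are not given.

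**The concern.** Mean decrease in Gini adds up the gain in node purity over all splits on a variable, in the data used to grow the trees. This has two consequences here.

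1. A variable with many possible cut points has many chances to find a split that looks useful by luck. A 0/1 code has one. Age therefore collects importance beyond what it adds to prediction.
2. Among the 0/1 codes, a common code can still be split on deep in the tree, where nodes are small and gains are mostly noise. An uncommon code soon runs out of patients to split. Common but uninformative codes can therefore rank above uncommon but predictive ones.

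A rare outcome makes chance gains larger relative to real ones. If clinicians are shown which conditions drive predicted AF risk, the order of the codes below age is what they will read, and that part of the ranking is the least secure.

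**Working it through.** The plan gives no figure on variable importance, so there is none to reproduce. The check has four steps.

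**1. Outcome frequency.** Data sources and permissions gives 4330 new cases among 2 159 663 CHS patients in six months: 4330 / 2 159 663 = 0.20%. No six-month rate is given for CPRD-GOLD, so 0.2% is used as an assumption.

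**2. Why common codes are favoured.** With minimum leaf size L, a node can be split on a code of prevalence p only if it holds about L / p patients or more (for p up to 0.5).
- L = 50: 50 / 0.03 = 1667 patients for a 3% code; 50 / 0.5 = 100 for a 50% code.
- L = 500: 500 / 0.03 = 16 667 against 500 / 0.5 = 1000.

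The common code is therefore available in many more small nodes. The leaf sizes and prevalences are assumptions.

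**3. Is age inflated?** Simulated forests, all inputs assumed: 40 000 patients, 80:20 split, 2% events, 100 trees, integer age 31 to 90, 20 independent binary codes with prevalence 1% to 50%, three seeds per cell. The equal share of importance is 1 / 21 = 4.8%. The last column is the mean loss of AUROC when age is permuted in the held-out 20%.

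| Truth | Min. leaf | Age, share of Gini | Age, Gini rank (3 seeds) | Held-out AUROC loss |
|---|---|---|---|---|
| Nothing predictive | 1 | 57% | 1, 1, 1 | -0.010 |
| | 50 | 45% | 1, 1, 1 | 0.015 |
| | 500 | 43% | 1, 1, 1 | 0.008 |
| Three codes only | 1 | 57% | 1, 1, 1 | -0.016 |
| | 50 | 30% | 1, 1, 1 | 0.001 |
| | 500 | 14% | 4, 4, 3 | 0.000 |
| Age strong (odds ratio 2.2 per 10 years) and three codes | 1 | 49% | 1, 1, 1 | 0.137 |
| | 50 | 70% | 1, 1, 1 | 0.261 |
| | 500 | 76% | 1, 1, 1 | 0.255 |

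Where age has no effect, Gini still gives it 14% to 57%. Where age is strong, it ranks first by both measures in 9 of 9 runs. Its share then moves between 49% and 76% with leaf size, so the share cannot be read as a fixed contribution.

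**4. Are the codes reordered below a strong age effect?** In step 3 with age strong, one seed was inspected for this. Both measures chose the same top four at minimum leaf 50 and 500. At minimum leaf 1, the Gini runners-up were commoner codes with no effect.

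That used 2% events, so the question was put again at 0.2%: 400 000 patients, 80:20 split, age with odds ratio 2 per 10 years, five true codes (prevalence 3% to 5%, odds ratio 2), 15 codes with no effect (prevalence 5% to 50%), three seeds. Expected held-out events are 0.20 x 400 000 x 0.002 = 160.
- Minimum leaf 50: all five places below age went by Gini to codes with no effect, in 3 of 3 runs. The true codes ranked 11th to 21st. A repeat gave 12th to 21st by Gini and mostly higher ranks by held-out permutation.
- Minimum leaf 500: codes with no effect held 4 to 5 of the top six places by Gini, against 1 to 2 by held-out permutation.
- Permutation was imperfect too, with 3 to 5 such codes in the top six at minimum leaf 50. It was equal or better in all six runs.

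Age ranked first by both measures throughout.

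**The case against.** Several points on the other side stand.

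- A reader might infer that the plan commits to publishing a Gini ranking. It does not. The wording says that importance can be calculated this way, and neither the validation sections nor the dissemination section lists a ranking as an output.
- A reader might infer that random forest was chosen because of this ranking. The stated reason is the systematic review, where the method had the most evidence and robust performance. Explainability is a supporting argument.
- A reader might infer that age would come first only as an artefact. The rows with an irrelevant age variable describe something the plan does not contain, since it treats age as relevant to AF. If age truly dominates, its first place is right.
- A reader might infer that the model itself is harmed. The logistic model uses "backward model selection with Akaike information criterion", the calculator rests on clinical rationale, and performance is judged by AUROC, Brier score, calibration, reclassification and decision curves. None of these uses Gini.
- Cross-validated tuning should steer away from the worst settings. In step 3 with age strong, AUROC was 0.676 at minimum leaf 1 and 0.817 at 50.
- Permutation importance has its own weakness: correlated codes share importance, and disease codes correlate with age and with each other.

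Two further arguments carry less weight. One is that 0/1 codes cannot be reordered among themselves because they all have two values. That holds for the number of values but not for prevalence, as steps 2 and 4 show. The other is that a condensed article may leave the importance measure to a fuller plan. A second measure may well be left there, but this article names one measure and gives it a purpose.

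**Conclusion.** The point holds as a minor one about interpretation. Any importance ranking reported by mean decrease in Gini would tend to overstate the relative share of age and to place common, uninformative codes above less common, predictive ones. The amount depends on the leaf size or depth that the grid search selects, so it can be neither fixed nor ruled out in advance. No prediction, performance measure, selected logistic model or calculator changes, and age keeps first place if it truly dominates.

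The simulations rest on assumed prevalences, effects and leaf sizes, on independent predictors and on fewer patients than the study will have. They show direction, not the size to expect in CPRD-GOLD. Where age is strong, they do not separate the inflated part of its share from the real part.

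**What to change.** In Prediction model development, replace the sentence on Gini with a commitment of this kind: variable importance will be reported as permutation importance in the held-out 20% sample, measured as loss in AUROC or log-loss, averaged over repeated permutations and given with intervals; the ethnicity indicators will be permuted together as one block; mean decrease in Gini may be shown as a secondary display. The intervals should also reflect resampling of the held-out patients, since repeating the permutation alone captures only part of the uncertainty. The text should caution that correlated codes share importance.

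The cost is some extra computing. No new data and no change to the model are needed, because the 80:20 split is already planned. Intervals will be wide for rare codes. Taking about 2 million patients before exclusions and the CHS rate as an assumption, held-out events number about 0.20 x 2 000 000 x 0.002 = 800. A code carried by 1% of patients and unrelated to AF would be present in about 8 of them.

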**Figure 2 F2:**
[figure not shown]
A schematic representation of a multivariable logistic regression model or random forest model using data from electronic health records to provide risk prediction for incident AF. AF, atrial fibrillation.

Preprocessed patient-level data in CPRD-GOLD will be randomly split into an 80:20 ratio to create derivation and internal validation (or training and testing) samples. The split ratio is not a significant factor, given the volume of the sample size. The model parameters and drop-out rate will be chosen through a grid search and 10-fold cross-validation will be used (ie, 10% of the training data will be randomly selected as the cross-validation set). The multivariable logistic regression model will be developed with backward model selection with Akaike information criterion.^37^ The prediction window will be set at 6 months, as this is considered in keeping with the logistical time frames for organising AF investigation at scale.

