## Methods and analysis

### Data sources and permissions

The derivation dataset will be the Clinical Practice Research Datalink-GOLD (CPRD-GOLD) dataset. This is an ongoing primary care database, established in 1987, which comprises anonymised medical records and prescribing data contributed by general practices using Vision software. It contains data for approximately 17.5 million patients, with 30% of contributing practices in England, and represents the UK population in terms of age, sex and ethnicity.^16^ In order to contribute to the database, general practices and other health centres must meet prespecified standards for research-quality data (‘up to standard’).^16 20^

Recorded information includes patients’ demography, clinical symptoms, signs, investigations, diagnoses, prescriptions, referrals, behavioural factors and test results entered by clinicians, and other practice staff. All clinical information is coded using Read Codes.^21^ Extracted patients will have patient-level data linked to Hospital Episode Statistics (HES), Admitted Patient Care (APC) and Office for National Statistics (ONS) Death Registration. The CPRD dataset has been used to develop or validate a range of risk prediction models.^22^

The extracted dataset, including linked data, comprises all patients for the period between 2 January 1998 and 30 November 2018 from the snapshot of CPRD-GOLD in October 2019. Over this study period, the CPRD-GOLD dataset comprises approximately 2 million patients eligible for data linkage at an up-to-standard practice, with over 200 000 patients having a record of AF during follow-up.

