#### Internal validation

We will evaluate the model performance using a validation cohort with internal bootstrap validation with 200 samples. The model will be applied to the testing dataset with the same predictor variables. The area under the receiver operating characteristic curve (AUROC) will be used to evaluate predictive ability (concordance index) with 95% CIs calculated using the DeLong method.^38^ Youden’s index will be established for the outcome measure as a method of empirically identifying the optimal dichotomous cut-off to assess sensitivity, specificity, positive predictive value and negative predictive value. We will calculate the Brier score, a measure of both discrimination and calibration, by taking the mean squared difference between predicted probabilities and the observed outcome. To assess the clinical impact of using prediction model as opposed to other risk prediction scores, we will calculate the case reclassification, non-case reclassification and overall net reclassification index at the risk threshold that equates to the average 6 months incidence rate in the cohort and conduct a decision curve analysis, which assesses across threshold probabilities whether the predictive model would do more benefit than harm. Calibration will be assessed graphically by plotting predicted AF risk against observed AF incidence and quantified using a calibration slope.

The same methods will be employed in subgroups by age (<65 years, ≥65 years, <75 years, ≥75 years), sex (women, men) and ethnicity (white, black, Asian, others and unspecified) to assess the model’s predictive performance across clinically relevant groups.

The performance of the prediction model will be compared with the CHA_2_DS_2_-VASc and C_2_HEST scores. The CHA_2_DS_2_-VASc score was originally developed to predict stroke risk in individuals with AF, and the C_2_HEST score for Asian people without structural heart disease.^19^ These algorithms are robust to missing data in routinely collected primary care EHRs and have been tested for AF risk prediction in European cohorts.^19^ Other algorithms that can only be applied to a minority of European primary care EHRs (Pfizer-AI, CHARGE-AF) will not be considered as they cannot be implemented at scale to inform AF screening.^17 27^

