#### Quantification of the association between short-term predicted AF risk and long-term AF and other diseases

We will include all patients randomly assigned to the testing dataset in CPRD-GOLD by the Mersenne twister pseudorandom number generator, categorised as lower or higher predicted AF risk by the developed prediction model at baseline (point of entry to the study). For long-term AF risk, we will plot Kaplan-Meier plots for individuals identified as higher and lower predicted risk of AF to assess the event rate for AF censored at 10 years, and calculate the hazard ratio (HR) for AF between higher and lower predicted risk of AF using the Cox proportional hazard model with adjustment for the competing risk of death. This will inform us of whether short-term AF risk is also associated with long-term AF risk, and whether an individual who undergoes risk-guided AF screening should be considered for repeated AF screening at a later time point (eg, 1 or 5 years).

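### The CPRD-GOLD split is random by patient, so the internal validation estimates average performance but never tests the model in UK practices unseen in training; splitting and resampling by practice is a cheap improvement

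*Protocol article*

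**What the plan says.** Under Prediction model development (text after Figure 2), the article plans that "Preprocessed patient-level data in CPRD-GOLD will be randomly split into an 80:20 ratio", which yields the training sample and the internal validation sample. The section on the association between predicted AF risk and other diseases confirms the unit of allocation: "We will include all patients randomly assigned to the testing dataset in CPRD-GOLD by the Mersenne twister pseudorandom number generator". Tuning uses 10-fold cross-validation, in which "10% of the training data will be randomly selected as the cross-validation set". Neither step is grouped by practice.

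Data sources and permissions describes the database as "anonymised medical records and prescribing data contributed by general practices using Vision software". Under Predictor variables, diseases and lifestyle factors are taken from codes, and "If medical codes are absent in a patient record we will assume that the patient does not have that diagnosis".

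Internal validation uses the test sample with "internal bootstrap validation with 200 samples". DeLong 95% intervals are specified for the AUROC, and calibration is assessed by a plot and a slope. Transportability is assigned to the Clalit Health Services (CHS) data under External validation.

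**The concern.** Patients in one practice share its recording habits. An absent code counts as an absent disease, so those habits enter the predictors directly. They enter the outcome in part, since AF is also found in hospital and death records. With a patient-level split, training and test samples are drawn from the same practices. The test sample can show whether the model overfits individuals, but not whether it holds up in a practice it has not met.

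The article's own sample-size reasoning makes that second question the more useful one. The derivation sample is several times the size required for a shrinkage factor of 0.95, so for the logistic model the overfitting that a random split detects should already be small.

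At stake are absolute risks. Net reclassification and decision curves are read at risk thresholds, and Ethics and dissemination foresees possible release through EHR platforms if performance and utility are shown. If calibration varies between practices, a pooled calibration plot and an AUROC interval that ignores clustering would not tell a reader how far a new UK practice might depart from the average.

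**Working it through.** **1. The plan's own figure.** Riley criterion 1 is n = P / [(S − 1) ln(1 − R²/S)]. With P = 200, R² = 0.01 and S = 0.95 (Sample size section), n = 377,996.5, which reproduces the stated 377,996. Putting n = 1,600,000 (80% of about 2 million) into the same formula and solving for S gives about 0.99. This point does not challenge the sample size. The result shows only that little overfitting is left for a random split to find in the logistic model.

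**2. Overlap of practices.** Under an 80:20 patient split, a practice with m patients has none in training with probability 0.2^m. For m = 10 this is about 1 in 10 million; for m = 500 it is about 10^−349. Practically every test patient comes from a training practice.

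**3. Can CHS stand in for unseen UK practices?** CHS records use ICD-9, whereas CPRD primary care uses Read codes. CHS predictor code lists are developed separately, and ethnicity is replaced by population sector and socioeconomic score. A calibration shift in CHS could not be attributed to practice, coding or country, and good calibration there would not show the spread across UK practices.

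**4. Size for observed/expected (O/E), under assumptions.**

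- Test patients: 20% of about 2 million = 400,000 (before any loss to the age and other exclusions).
- Events: the article gives no CPRD six-month rate. Borrowing the CHS rate, 4330 / 2,159,663 × 400,000 ≈ 802. This is an assumption.
- Practices K = 200 to 400, and between-practice SD of AF log-odds after the predictors, τ = 0.2 to 0.4. Neither is in the article; both are assumptions.
- SE ignoring clustering: 1/√802 = 0.0353.
- SE with a fifth of practices held out: √(0.0353² + τ²/(0.2K)).

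| K | τ | SE | Ratio to 0.0353 |
|---|---|---|---|
| 400 | 0.2 | 0.042 | 1.18 |
| 400 | 0.3 | 0.049 | 1.38 |
| 400 | 0.4 | 0.057 | 1.61 |
| 200 | 0.2 | 0.047 | 1.34 |
| 200 | 0.3 | 0.059 | 1.67 |
| 200 | 0.4 | 0.072 | 2.05 |

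The factor is therefore about 1.2 to 2.1. It belongs to a test in 40 to 80 held-out practices. If all K practices stay in the test set, as planned, replacing 0.2K by K gives only 1.04 (K = 400, τ = 0.2) to 1.28 (K = 200, τ = 0.4). Part of the larger factor is thus the price of testing in fewer, unseen practices.

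**5. Is mean discrimination inflated?** A simulation with logistic regression, 400,000 patients, practice-varying incidence and coding sensitivity, and an AF rate of about 0.9% (8 runs per setting) compared the two splits.

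| K | Variation | Mean AUROC, patient v practice split | Run-to-run SD of O/E, patient v practice split |
|---|---|---|---|
| 200 | moderate | 0.858 v 0.863 | 0.041 v 0.036 |
| 200 | strong | 0.861 v 0.858 | 0.054 v 0.112 |
| 400 | moderate | 0.858 v 0.859 | 0.038 v 0.043 |
| 400 | strong | 0.855 v 0.857 | 0.029 v 0.072 |

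Mean AUROC differs by less than 0.005, in both directions. O/E is clearly more variable in held-out practices only under strong variation (τ = 0.4). Eight runs give rough SDs, and a random forest was not simulated.

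**The case against.** The article calls this step internal validation and makes no claim that it shows performance in new practices; it plans a separate external validation. No practice identifier is among the listed predictors, contributing practices must meet a data-quality standard, and AF is also ascertained outside primary care. All of this stands, and it limits the point to an improvement.

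Four stronger readings are tempting, and the documents do not support them.

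- A reader might infer that internal performance says nothing about a new practice. It still estimates the average over many practices, and the simulation showed no systematic inflation of AUROC.
- A reader might infer that a patient split hides the between-practice spread. It need not: O/E can be tabulated by practice in either kind of test set. In a second illustrative simulation (400,000 patients, logistic model, 12 runs per setting), the between-practice variance of O/E at τ = 0.4 was 0.155 (patient split) against 0.151 (practice split) with 400 practices, and 0.131 against 0.147 with 200.
- A reader might infer that the intervals for calibration and positive predictive value are too narrow. The article specifies an interval method only for the AUROC, and O/E is not a listed metric. The factor in the working illustrates calibration-in-the-large and does not carry over to the AUROC interval.
- A reader might infer that 200 bootstrap samples are too few. That would matter if they supplied percentile limits, which the article does not say.

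One practical objection also stands. Some 802 events over 40 to 80 test practices is about 10 to 20 each, too few for a stable AUROC in each practice.

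**Conclusion.** The point holds as a cheap improvement to a stated method. The split and the tuning folds are random by patient, so no planned analysis tests the model in UK practices unseen in training. The DeLong interval ignores clustering, and CHS answers a different question. The consequence concerns calibration across practices and interval width; no bias in mean AUROC is shown. Under the assumed practice numbers, between-practice SD and borrowed event rate, the standard error of log(O/E) in held-out practices is about 1.2 to 2.1 times the value that ignores clustering. With smaller between-practice variation or more practices the factor moves towards 1. Whether a random forest with many code predictors would pick up practice-specific patterns more readily than logistic regression remains untested.

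**What to change.** In Prediction model development, allocate whole practices 80:20 to derivation and testing, and form the ten tuning folds by practice. In Internal validation, compute confidence intervals, including that for the AUROC, by resampling practices, and report the between-practice spread of observed/expected. Where events per practice are few, pool practices or use regions as the unit.

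No new data are needed, since the records come from identifiable contributing practices. The cost is somewhat wider intervals and modest extra work: regrouped folds, a cluster bootstrap and one between-practice summary.
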